#### Data analysis

Data analysis will be carried out according to an analysis protocol following the "intention to treat principle." The primary analysis will be a comparison of the levels of fatigue in the intervention and the control groups and their changes over the course of time. Logistic regression models and variance analyses will be used to determine the impact/effect modification of secondary outcomes and to control for possible differences between the groups. All significance tests will be two-tailed and chosen allowing for scale levels.

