#### Data Collection and Outcome measures

Data will be collected three times by self-rated measures: Baseline data will be collected before patients are randomized to one group. The second measurement will take place each time after an intervention has taken place for the intervention and its associated control group. A follow-up will be carried out six months later.

Fatigue is the primary outcome measured by the Fatigue Assessment Questionnaire (FAQ) [33]. The instrument differentiates between physical, cognitive and affective fatigue and defines the level of fatigue on a scale from 0 to 60.

Secondary outcomes to test the behavioral impact of the intervention are general self-efficacy [34], self-efficacy of physical activity [35], levels of physical activity [36], and knowledge about fatigue and its therapy.

Further outcomes which are potentially related to/affected by fatigue are anxiety and depression measured by the German version of the hospital anxiety and depression scale (HADS) [38] and quality of life by the EORTC QLQ-C30 [39].

To control for differences between the groups and possible confounders, several sociodemographic variables and medical background information are also recorded.

Outcomes are measured at three different points in time: before randomization; after completion of the program, which is about six weeks later; and after a follow-up at six months.

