#### Sample size considerations

In terms of detecting a difference in FAQ scorings of 4 points with a median of 15 (alpha = 0.05; beta = 0.2) and 25% estimated rate of drop-outs, 300 patients (150 in each group) have to be recruited; therefore, about 19 randomization processes, as described above, have to be carried out over the entire term in order to assemble groups of 8 participants.

The effect size d was calculated as a result of inconsistent presumptions regarding the other outcomes describing the expected effects and standard deviations. If 300 patients are included, a small to moderate effect size of 0.35 can be detected in a two-tailed test setting alpha = 0.05 and beta = 0.2, which is assumed to be satisfactory.

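### The primary analysis pairs fatigue levels with changes over two post-baseline visits, names no deciding comparison, and does not name baseline FAQ as a covariate

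*Protocol article*

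**What the plan says.** The FAQ, scored 0 to 60, is the primary outcome (Data Collection and Outcome measures). It is measured three times: "before randomization; after completion of the program, which is about six weeks later; and after a follow-up at six months". On the first of these, the same section says: "Baseline data will be collected before patients are randomized to one group".

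The Data analysis section describes the primary analysis as "a comparison of the levels of fatigue in the intervention and the control groups and their changes over the course of time". It then plans logistic regression and variance analyses, in part "to control for possible differences between the groups". It also says: "All significance tests will be two-tailed and chosen allowing for scale levels". The section opens by referring to a further document: "Data analysis will be carried out according to an analysis protocol". That document is not shown.

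Sample size considerations bases the 300 patients on one FAQ difference of 4 points, with alpha 0.05, beta 0.2 and 25% dropout. It does not say whether the 4 points are a difference in level or in change, or at which visit. The first prediction, at the end of the Background, is that the program significantly lowers the level of fatigue.

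**The concern.** One primary label covers two quantities, level and change, and each can be taken at about six weeks or at the six-month follow-up. The article powers one difference at one alpha but does not say which of these comparisons the first prediction stands or falls on. If the choice stays open, a positive conclusion could rest on whichever comparison succeeds, and the error rate behind it is not shown to be 5%.

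The second issue is precision. The baseline FAQ is collected before randomisation and is likely to predict the later score. A raw level ignores it, and a change score subtracts all of it. The article does not name it as a covariate, which would be the more precise use.

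**Working it through.** **The plan's own figure.** The 300 cannot be reproduced for the 4-point difference, because a median of 15 is given but no SD. With 25% dropout, 300 × 0.75 = 225 complete, or 112.5 per arm. The detectable standardised difference is then (1.960 + 0.842) × √(2/112.5) = 0.374, which implies an SD of 4/0.374 ≈ 10.7. The d of 0.35 in the same section needs 2 × (1.960 + 0.842)² / 0.35² = 129 completers per arm, so 129/0.75 = 172 per arm and 344 recruited. That mismatch is a separate matter and does not decide this point. Below, d = 0.35 is used for the FAQ as an assumption; for 4 points it corresponds to an SD of 4/0.35 ≈ 11.4.

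**False-positive rate if any nominal 0.05 test may count.** For independent tests the rates are 1 − 0.95² = 9.75% (two) and 1 − 0.95⁴ = 18.5% (four). The actual tests are correlated, so the rate was simulated under no effect, with 2,000,000 draws per setting. Visit correlations of 0.3, 0.5 and 0.7 were assumed, with equal-correlation and autoregressive patterns, because the article gives none.

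| Tests that could count | Chance of at least one false positive |
|---|---|
| One fixed test | 5% |
| Levels at both visits | 8.4–9.5% |
| Level and change at one visit | 8.7–9.4% |
| Levels and changes at both visits | 15.3–16.0% |

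**Precision.** Let ρ be the correlation between baseline and follow-up FAQ, with equal variances at both visits. Relative to the raw level, the variance factors f are:
- level: 1
- change: 2(1 − ρ)
- baseline-adjusted (ANCOVA): 1 − ρ²

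ANCOVA is below the level by ρ² and below the change by 2(1 − ρ) − (1 − ρ²) = (1 − ρ)². It is therefore the smallest of the three for every ρ between 0 and 1.

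**Power.** With n = 112 per arm, power = Φ(0.35/√f × √(112/2) − 1.960). For the level, 0.35 × 7.483 = 2.619, and Φ(0.659) = 74.5% (74.1% with the t distribution). For ANCOVA at ρ = 0.5, 2.619/√0.75 = 3.024, and Φ(1.064) = 85.6%.

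| Assumed ρ | Level | Change | ANCOVA |
|---|---|---|---|
| 0.3 | 74.5% | 60.0% | 78.4% |
| 0.5 | 74.5% | 74.5% | 85.6% |
| 0.7 | 74.5% | 92.2% | 95.6% |

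Completers needed per arm for 80% power at d = 0.35 are 129 for the level; 180, 129 and 77 for the change; and 117, 97 and 66 for ANCOVA, at ρ of 0.3, 0.5 and 0.7.

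**The case against.** The strongest reply is that this is a condensed article that refers to an analysis protocol, and that the exact model, covariates and testing order may sit there. The wording speaks of a single comparison. With three measurements and variance analyses planned, it could mean one repeated-measures or group-by-time test, which would hold 5%. This has force: the error rates above are conditional, and a reader who infers that the plan does inflate the false-positive rate goes further than the text. The article nowhere says that any one success is enough.

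Two other strong readings also fail. A reader might infer that there is no baseline adjustment. The article plans models to control for group differences, and it neither names nor excludes baseline FAQ. A reader might also infer that the baseline FAQ is wasted, but a comparison of changes uses it, only less efficiently.

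It is also fair to say that a less efficient estimator is not an error, since all three are unbiased in a randomised comparison. The size of the gain depends on an assumed correlation: at ρ = 0.7 ANCOVA adds little to the change score. The power of 74.5%, below the stated 80%, comes from dropout and not from the choice of analysis.

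What remains is that the article does state a primary analysis, and states it as levels together with changes. That is a badly fixed statement, not merely a detail left out, and the sample size on one difference depends on which comparison is meant.

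**Conclusion.** The point holds in limited form. The stated primary analysis fixes no deciding contrast or visit, so control of the false-positive rate at 5% is not shown. The rate would be 8.4–9.5% for two tests and 15.3–16.0% for four, but only if any nominal success could count, and with visit correlations of 0.3 to 0.7.

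Baseline FAQ is not named as a covariate, and both stated comparisons are less precise than a baseline-adjusted one for any correlation between 0 and 1 with equal variances. At correlations of 0.3 to 0.5, with d = 0.35 assumed for the FAQ and 112 completers per arm, adjustment adds about 4 to 11 percentage points of power over levels (78.4 − 74.5 and 85.6 − 74.5) and about 18 to 11 over changes (78.4 − 60.0 and 85.6 − 74.5). The correction is worth making because it costs almost nothing.

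**What to change.** Define the primary analysis as one contrast: the difference between arms in FAQ total (0–60) at one named post-baseline visit, from a linear model adjusted for baseline FAQ total, tested two-sided at 0.05. State that the 4-point difference in the sample size refers to this contrast. Test the other visit second, with the same model at 0.05, only if the first test succeeds. Report change scores as supportive. If the analysis protocol already fixes a single test, bring the article's wording into line with it.

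The change affects the analysis wording only; no further patients or measurements are needed. Its downside is that an effect at the second visit cannot be claimed if the first test fails. Splitting alpha avoids that but costs more: at 0.025 per visit and d = 0.35, an unadjusted comparison needs 156 completers per arm (156/0.75 = 208, so 416 recruited), and power at 112 per arm falls to 64.7%.

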### Ethical considerations

Full ethical approval for this study has been obtained by the ethical committee of the University of Bremen, Germany.

### Time plan

Development and formative evaluation of the intervention began in April 2007 and was finished in January 2008. Patient recruitment therefore began in February and will continue until February 2010. The study will be completed in June 2010.

## Discussion

FIBS is expected to be an effective intervention to control fatigue by achieving behavioural changes in disease-free cancer patients.

## Abbreviations

CRF: Cancer-related Fatigue; FIBS: Fatigue individuell bewältigen – ein Selbstmanagementprogramm (Coping with fatigue individually – a self-management-program); FAQ: Fatigue Assessment Questionnaire; HADS: Hospital anxiety and depression scale.
